## Results

The study began in April 2018 and will continue until March 2026. Patients and the public are not directly involved in establishing the research question, study design, outcome measures, recruitment, or conduct of the study. Tables will be prepared for the endpoints; the exact 95% confidence intervals of the binomial distribution will be calculated for each group to compute percentage estimates.

It is hypothesized that the osteolysis of the DSO imaging findings would be associated with symptoms such as pain. It is expected that zoledronate administration, a potent bone resorption inhibitor, will reduce pain by decreasing the osteolysis area. The amount of change in pain before and after the administration of zoledronate is assessed; the closer the VAS value approaches 0 after zoledronate administration, the stronger the pain-suppressing effect of zoledronate on DSO is explained. The change in pain over time is expressed graphically. Moreover, it is expected that zoledronate has an immediate effect on DSO if the pain suppression effect develops early after administration. Concomitantly, if CT images after zoledronate administration show a decrease in the osteolysis area, the decrease in osteolysis is considered to be due to zoledronate administration. In addition, zoledronate is an existing medicine, which explains the safety of zoledronate in patients with DSO if zoledronate administration does not cause serious side effects.

The results of this study will be published in a peer-reviewed international journal. We also plan to present at a scientific meeting to share the results with other researchers in Japan.

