## Abstract

Introduction: Diffuse sclerosing osteomyelitis (DSO) is a non-bacterial osteomyelitis that occurs infrequently and is characterized by recurrent severe pain, swelling of the mandible, and trismus. To date, no effective treatment has been established. Bisphosphonates have been suggested as an efficacious treatment for DSO; however, no prospective studies have examined the effect of bisphosphonate treatment in adults with DSO. This study aims to evaluate the effect of zoledronate on pain suppression in patients with DSO.

Methods: This is a single-center, exploratory, single-arm, prospective interventional study. The participants will include eight patients with DSO of the mandible. The primary endpoint is the change in pain levels before and after zoledronate administration. The secondary endpoints are assessing the efficacy of the clinical course, imaging changes, and safety monitoring. Patients will be enrolled if they are deemed eligible following screening tests and will receive only one 4.0 mg intravenous dose of zoledronate within seven days of enrollment. Study participants will be followed up at one, four, 12, 24, and 48 weeks post-dose or at discontinuation after zoledronate administration.

Conclusion: This study is the first prospective trial to evaluate the effect of administering a single dose of zoledronate on pain suppression in patients with DSO. We believe this study will lead to the conclusion that zoledronate is an effective treatment for DSO.

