## Materials and methods

Study design and setting

This exploratory, single-arm, prospective interventional study will only be conducted at Kobe University Hospital. The study will be conducted in a single-arm setting due to difficulties in securing a sufficient sample size owing to disease rarity and lack of standard treatment, as well as its status as a pilot trial for future research.

Patient selection

This study will include patients who meet all the following inclusion criteria. The inclusion criteria include patients aged 20-80 years at the time of consent to participate; diagnosed with DSO based on clinical symptoms, panoramic radiography, mandibular computed tomography (CT), magnetic resonance imaging (MRI), and blood test findings [2]; and who give their free and voluntary written consent to participate in this clinical study.

The exclusion criteria are patients without a diagnosis of DSO based on clinical symptoms, panoramic radiography, mandibular CT, MRI, and blood test findings and with a serum-corrected calcium (Ca) level of ≤8.6 mg/dL determined by a blood test before zoledronate administration. The exclusion criteria also include patients with hepatic dysfunction (serum aspartate aminotransferase (AST) or alanine aminotransferase (ALT) level ≥ 70 IU/L or total bilirubin (T-Bil) ≥ 2.0 mg/dL) and with renal dysfunction (estimated glomerular filtration rate (eGFR) < 30 mL/min). Patients with allergies or other drug sensitivities; a history of QT prolongation, seizures, tetany, numbness, and disorientation associated with hypocalcemia; and MRONJ or a history of MRONJ are also excluded from the study. The exclusion criteria also include patients with the following risk factors for MRONJ: malignancy, angiogenesis inhibitors, corticosteroid therapy, and radiation therapy; with symptoms of otitis externa, ear leakage, or ear pain; and on calcitonin preparations, aminoglycoside antimicrobials, or cinacalcet. Pregnant women and patients who may be pregnant or nursing, patients who participated in another clinical study within four months of participating in the current study, and patients deemed inappropriate for inclusion in the study by the investigators in charge of this clinical research are also excluded from the study.

Interventions

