**Table 1 TAB1:** Implementation schedule and procedures ○: items to be performed before zoledronate administration; ■: zoledronate administration; ​​​​​​​●: items to be performed following zoledronate administration; ​​​​​​​*: concomitant use of analgesics, including non-steroidal anti-inflammatory drugs and/or antimicrobials

	Screening test	Date of administration	Observation period				
Time point	Before 1 week	0	After 1 week	After 4 weeks	After 12 weeks	After 24 weeks	After 48 weeks
Consent acquisition	○						
Check patient background	○						
Zoledronate administration		■					
Check of subjective and objective symptoms	○	●	●	●	●	●	●
Observation of side effects	○	●	●	●	●	●	●
Vital sign measurement	○	●	●	●	●	●	●
Weight measurement	○	●	●	●	●	●	●
Blood tests conducted	○		●	●	●	●	●
Panoramic radiography conducted	○					●	●
Computed tomography conducted	○					●	●
Concomitant therapy administered^*^	○	●	●	●	●	●	●

Sample size

The target number of participants is eight. Among the reasons for this setting is that the frequency of DSO is extremely low, and only six patients have been administered zoledronate in the past two years in our department. In addition, this clinical study has an exploratory aspect; therefore, the target number of eight cases is considered reasonable. According to the report by Otto et al. [18], a rationale for setting this parameter is that if the changes in the means and standard deviations of the VAS are considered to be six, a one-sample t-test with a significance level of 5% (two-tailed) would yield a power of 80% in eight cases.

Data collection and management

In this clinical study, the clinical research database and clinical research-related documents will be associated with the original data of the research participants using a list of research participant identification numbers. The principal investigator or sub-investigator will prepare a case report form (CRF) for each research participant. The CRF will include the date on which participant consent was obtained, participant identification number, sex, date of birth, age at consent, date of observation, subjective and objective symptoms, vital signs, weight, imaging findings, and blood test results.

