The radiographic findings of DSO show an osteolytic area that is considered to be responsible for causing clinical symptoms such as pain and swelling [1]. Since a histological study of patients with acute-phase DSO has suggested that many osteoclasts develop and produce cathepsin K [23], the osteolytic area is probably a site of over-activated osteoclasts. The mechanism through which DSO develops is not yet clear; however, suppressing activated osteoclasts may lead to symptom alleviation. Since bone resorption inhibitors such as bisphosphonates inhibit osteoclasts, they may exert a pain suppression effect in patients with DSO by affecting the osteolytic area. No treatment regimen for DSO has been established; however, we believe this study will lead to zoledronate being an effective treatment for DSO.

The main limitation of this study protocol is the lack of a set control group. Although a comparison with a placebo control would be more beneficial, the rarity of the disease makes recruiting a sufficient number of patients difficult. Therefore, although the study will be conducted as a single-arm study, the potential placebo effect cannot be completely ruled out. Alternatively, comparison with historical controls may be useful; however, it will not be considered in this study as there is currently no established treatment for DSO other than symptomatic treatment. Future research efforts will build on the results found in this study and aim to accumulate more cases and expand the scope through multicenter studies.

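### The Results section plans to read a CT decrease in osteolysis as caused by zoledronate, and an absence of serious side effects as explaining its safety; eight uncontrolled patients support neither

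*Protocol article*

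**What the plan says.** The relevant text is in the second paragraph of the Results section of the protocol article, which describes how findings will be understood once they are in.

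- **CT.** If post-treatment images show a smaller osteolytic area, "the decrease in osteolysis is considered to be due to zoledronate administration".
- **Safety.** Zoledronate is described as a medicine that already exists, "which explains the safety of zoledronate in patients with DSO if zoledronate administration does not cause serious side effects".

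Neither sentence carries a qualifier.

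On design, the Materials and methods section states: "This exploratory, single-arm, prospective interventional study will only be conducted at Kobe University Hospital". It also calls the study a pilot for later research. Under Sample size: "The target number of participants is eight". The Discussion says "The main limitation of this study protocol is the lack of a set control group". Of a historical comparison it says "it will not be considered in this study as there is currently no established treatment for DSO" beyond symptomatic care. Analgesics and antimicrobials may be given as needed for the whole study (Patient clinical management and follow-up; Table 1). The Discussion also names MRONJ as a serious bisphosphonate harm that remains a worry even after one dose.

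**The concern.** Both sentences turn a descriptive result into a claim that the design cannot carry.

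The CT sentence is causal. A before-after change in one arm combines any drug effect with the natural course of the disease, regression to the mean and the effect of co-treatment. Nothing in the plan separates these.

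The safety sentence treats the absence of an observed event as informative about patients with DSO, for whom use is off-label. With eight patients, that absence would be unsurprising even if serious harm were fairly common.

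The article plans publication in an international journal, so both readings could be carried into the report of a rare disease with no established treatment, where one small study may weigh heavily.

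**Working it through.** **Is there a planned figure to reproduce?** Not for safety or CT. The only quantitative sample-size argument concerns pain: mean change 6, SD 6, two-sided 5%, 80% power. The normal approximation gives n = ((1.960 + 0.842) × 6/6)² = 7.85, rounded up to 8, which matches the target. Whether that approximation suits the planned t-test is a separate matter. The calculation says nothing about the precision of a side-effect rate.

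**Safety: inputs.**
- n = 8 (Sample size).
- Exact binomial 95% intervals for percentages (Results).
- Six earlier in-house patients with no serious adverse events (Introduction).
- True serious-event rate: not given. Assumed range 5% to 20%, for illustration only.

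**Safety: upper limit with zero events.** The exact two-sided 95% upper limit for 0/n is 1 − 0.025^(1/n).
- n = 8: 1 − 0.025^(1/8) = 1 − 0.6306 = 36.9%. The one-sided 95% limit is 1 − 0.05^(1/8) = 31.2%.
- n = 14, adding the six earlier patients: 1 − 0.025^(1/14) = 1 − 0.7684 = 23.2%. This takes the two groups as comparable in selection, follow-up and event recording.

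**Safety: chance of seeing no event in eight.** This is (1 − p)^8.

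| Assumed true rate p | Chance of 0 in 8 |
|---|---|
| 5% | 0.95^8 = 66% |
| 10% | 0.90^8 = 43% |
| 20% | 0.80^8 = 17% |

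**Safety: size needed.** With zero events, a two-sided 95% interval that excludes a rate p needs n ≥ ln(0.025)/ln(1 − p): 36 patients for 10% and 72 for 5%.

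**CT: no arithmetic applies, so the statements are set side by side.**
- Results: a decrease is due to the drug.
- Materials and methods, Discussion: one arm, no control group, no historical comparison.
- Introduction: the disease is recurrent, and many patients relapse soon after improving on symptomatic treatment. The Results and Discussion link the osteolytic area to symptoms. If that link holds, an area that follows a fluctuating course may itself fluctuate without zoledronate.
- Patient clinical management and follow-up: antimicrobials and NSAIDs are allowed throughout. The Discussion cites complete remission in 19% with antimicrobials and 2% with anti-inflammatory drugs. It does not say whether that remission includes imaging, so these figures show only that the article itself credits co-treatment with some effect.

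The first statement cannot be drawn from a study described by the other three.

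**The case against.** The best defence is that these sentences are narrative, not analysis. The Statistical analysis section sets a single test, on change in VAS. For the rest it plans estimates with intervals and graphs, and it defines no success criterion for CT or safety. A reader might infer that formal decision rules have been fixed; the documents do not support that. What they contain is a stated reading of results, and that reading is still unsupported.

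Second, the safety sentence does not rest on eight patients alone, because its premise is that zoledronate is already in use. That stands, and the 0/8 interval is not a complete test of the sentence. But the sentence speaks of patients with DSO, and experience in other indications does not make eight of them more informative about this population.

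Third, the article has caveats. The exact interval is planned, MRONJ is still named as a worry, and the missing control group is admitted. These are real, but none is attached to either sentence.

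Two further inferences should be resisted. The Discussion concedes that "the potential placebo effect cannot be completely ruled out". A reader might set this directly against the CT sentence, but it bears mainly on self-reported pain; the admitted lack of a control group is the relevant point for CT. The Abstract's "We believe this study will lead to the conclusion that zoledronate is an effective treatment for DSO" might be read as a pre-written efficacy conclusion. It is a statement of belief and does not say how data will be interpreted.

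**Conclusion.** The point holds as one about stated interpretation. It affects what the trial may conclude on CT and safety; the primary pain analysis does not change.

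For safety, zero serious side effects in eight patients would be compatible with a true rate of up to 36.9%, or 23.2% with the six earlier patients pooled. These limits depend only on n and on independence between patients, with the comparability of the two groups added for the pooled figure. The 66% to 17% chance of no event depends on the assumed 5% to 20% range and is not an estimate for zoledronate. In particular, it is not tied to MRONJ: the article knows of no case after a single dose, and patients with MRONJ, a history of it or listed risk factors are excluded.

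A reader might also infer that no serious event is the most likely result. The documents give no rate to support this. It would be more likely than not only if the per-patient rate were below 1 − 0.5^(1/8) = 8.3%.

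For CT there is no number to correct. Attribution to the drug is outside what an uncontrolled before-after comparison can show.

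**What to change.** Reword two sentences in the Results section.

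- **Safety:** *The number and percentage of patients with serious side effects will be reported with the exact 95% confidence interval as preliminary safety data. No events in eight patients (upper limit 36.9%) would not establish safety in DSO.*
- **CT:** *Changes in osteolysis will be described as observed after zoledronate. Without a control group they will not be attributed to it.*

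No new data, visits, patients or analyses are needed, since the exact interval is already planned. The changes also bring the section into line with the exploratory, pilot purpose stated in Materials and methods and with the larger multicentre work foreseen in the Discussion. The only cost is a less favourable claim.

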## Discussion

The main objective of this study is to determine the efficacy of administering a single dose of zoledronate to suppress pain in patients with DSO. To the best of our knowledge, no prospective studies have suggested the efficacy of zoledronate in the treatment of DSO; thus, this is the first trial.

According to the recent systematic review [6], NSAIDs provide early symptomatic improvement in DSO of the mandible; however, the complete remission rate for anti-inflammatory drugs including steroids is 2%. In addition, the complete remission rate is 19% for antimicrobials, including long-term macrolide therapy. On the other hand, bone resorption inhibitors are more effective for DSO of the mandible (the complete remission rate, 45%). Most of the bone resorption inhibitors reported to be effective in DSO treatment are bisphosphonates, particularly pamidronate, a non-cyclic-type nitrogen-containing bisphosphonate [7,10,11,13,14,19,20]. All reports of pamidronate administration for treating DSO were case reports or retrospective case-control studies, and the doses and number of administrations differed. In many cases, the effect was achieved within a few days of the start of the administration of the agent, and multiple doses were administered. Zoledronate, a cyclic-type nitrogen-containing bisphosphonate, has been reported to inhibit bone resorption more than 300 times more potently than pamidronate [21]. Therefore, we hypothesized that only one dose of zoledronate might be effective for treating DSO. In a preliminary study, we administered zoledronate to six patients with DSO. We found that pain resolved within 24 hours after administration in most patients, with no symptom relapse observed after only a single dose. Thus, we designed the current study.

MRONJ is a serious side effect of bisphosphonates [9]. Bisphosphonate-induced MRONJ is likely to occur with long-term intravenous administration [9,22], but to our knowledge, MRONJ has not been reported to occur after only one dose of zoledronate. Therefore, administering a single dose of zoledronate to treat DSO could show benefits in terms of the occurrence of side effects, even though MRONJ development would still be of concern.

The radiographic findings of DSO show an osteolytic area that is considered to be responsible for causing clinical symptoms such as pain and swelling [1]. Since a histological study of patients with acute-phase DSO has suggested that many osteoclasts develop and produce cathepsin K [23], the osteolytic area is probably a site of over-activated osteoclasts. The mechanism through which DSO develops is not yet clear; however, suppressing activated osteoclasts may lead to symptom alleviation. Since bone resorption inhibitors such as bisphosphonates inhibit osteoclasts, they may exert a pain suppression effect in patients with DSO by affecting the osteolytic area. No treatment regimen for DSO has been established; however, we believe this study will lead to zoledronate being an effective treatment for DSO.

The main limitation of this study protocol is the lack of a set control group. Although a comparison with a placebo control would be more beneficial, the rarity of the disease makes recruiting a sufficient number of patients difficult. Therefore, although the study will be conducted as a single-arm study, the potential placebo effect cannot be completely ruled out. Alternatively, comparison with historical controls may be useful; however, it will not be considered in this study as there is currently no established treatment for DSO other than symptomatic treatment. Future research efforts will build on the results found in this study and aim to accumulate more cases and expand the scope through multicenter studies.

## Conclusions

This study is the first prospective trial to evaluate the effect of administering a single dose of zoledronate on pain suppression in patients with DSO. Since acute symptoms of DSO are considered to be associated with areas of osteolysis, and zoledronate is a potent bone resorption inhibitor, we hypothesized that zoledronate would be a highly effective agent to treat DSO. We believe this study will lead to zoledronate being an effective treatment for DSO.
